### 1.2 Trial Rationale

This study has been designed in response to a commissioned call by the National Institute for Health Research (NIHR) Health Technology Assessment (HTA) programme (see Appendix X for Commissioning Brief).

The best route of steroid delivery for hearing recovery in ISSNHL is unknown. Optimising treatment for ISSNHL is important for both participants and health resources as the condition results in reduced quality of life (4). Patient and Public Involvement (PPI) work by the trial team also identified a need for better diagnosis and access to specialist care if the management and hearing outcomes of individuals with ISSNHL are to be improved.

Members of our participant group have described that frequently, delay in diagnosis resulted in stress and anxiety that their hearing outcome could have been compromised. This is poorly represented in published studies on ISSNHL. Two main challenges in improving functional hearing recovery for participants with ISSNHL were identified:

- 1) Uncertainty around the most effective route of steroid administration
- 2) Delays in GPs identifying ISSNHL and arranging specialist care

While the first challenge is the main aim of the trial, we will also explore the second aim within the remit of this trial. The trial team have formed a GP advisory group, consisting of GPs and GP trainees (with and without clinical trials experience), with the aim of improving GP identification of ISSNHL and referral. Together with the Primary Care Academic Collaborative,

---

the team have designed action plans to maximise GP awareness, assessment and management of ISSNHL, which should aid referral and thus participant recruitment in the trial.

### 1.2.1 Justification for participant population

The target population in this trial is limited to adults with no upper age restriction. This is because ISSNHL is very rare in children, they have a different risk-profile to adults and there are implications around the practicalities of oral and intratympanic steroid use in children. .

The trial population includes women of child bearing potential. As with all drugs, corticosteroids should only be prescribed to pregnant women when the benefits to the mother and child outweigh the risks. Short-course high dose steroids are a low risk intervention in pregnant women. While old data had suggested that systemic corticosteroid use during pregnancy increases the risk of cleft lip/palate, preterm birth or low birth weight (5), recent studies have confirmed there is no independent association seen in the US National Birth Defect prevention Study (6,7). Maternal risks of corticosteroid specific side-effects such as hyperglycaemia and hypertension are similar to non-pregnant patients (e.g.) (8). Therefore, pregnant women are not excluded from this study. A discussion of the risks and benefits of steroids in pregnancy should take place if the study participant could be pregnant, as is standard clinical practice.

Participants with an identified cause for hearing loss or bilateral ISSNHL will be excluded as the intervention arms may not represent best care. Those with prior steroid treatment for the same episode of ISSNHL will also be excluded due to the risk of confounding treatment effects. Ipsilateral acute or chronic middle ear disease including acute otitis media, chronic suppurative otitis media and cholesteatoma will lead to exclusion as injected steroids may not reach the inner ear.

### 1.2.2 Justification for design

STARFISH is a three arm, superiority randomised, controlled trial. The three arms reflect the variation in current practice and the trial aims to elucidate which of these three arms is the optimal (superior) treatment. Randomised controlled trials are considered “gold standard” for evidence-based medicine.

Procedurally, the trial is designed to be in line with standard clinical practice as much as possible, to minimise burden on participants. The four week recruitment window from symptom onset reflects current practice, where more than half of UK surgeons would use intratympanic steroids up to one month after onset (9). Two meta-analyses suggest that the final hearing threshold may be independent of the delay in steroid treatment, for both primary (10) and secondary therapy (11), supporting the four-week treatment window, which is longer than some other trials adopt.

PPI suggested concern over recovery of hearing outweighs the anxiety associated with more invasive intratympanic steroid treatment, with randomisation acceptable to 80% of those surveyed. Reasons for the chosen minimisation variables include: there is a correlation between the hearing threshold before treatment and recovery (10); progressive spontaneous recovery may mean those treated later have already undergone some recovery; vertigo is a poor prognostic indicator (33).

---

Patient and public involvement in trial design led to the adoption of many of the outcome measures, including speech, tinnitus and dizziness questionnaires, and the optional participant-led home testing. The use of a modified classification system for recovery was suggested by participants, allowing the audiogram data to be translated into more relevant and meaningful measures to participants.

### 1.2.3 Choice of intervention

Oral steroid (Prednisolone) is included as an intervention as this is recommended in US guidelines (1), and used by most ENT clinicians across the UK (9,14). As the current standard of care, this represents control intervention.

Intratympanic steroid (dexamethasone) is included as a recent survey suggested 62% of UK ENT surgeons use intratympanic steroid injection in the treatment of ISSNHL (9) with dexamethasone the most commonly used steroid. 80% of surgeon's space injections 2-7 days apart (9), leading to the trial recommended schedule.

The third intervention is combined oral and intratympanic steroids, with the first intratympanic injection occurring within a period  $\pm 4$  days of starting oral steroids.

Meta-analysis shows no evidence that one intratympanic steroid regime is superior (10), and so the most commonly used agent (dexamethasone) and frequency of injection (three) in the UK have been adopted. For the one third of ENT surgeons not currently using intratympanic injection for ISSNHL, the technique is easy to learn. The trial team will assist in training surgeons either remotely via videoconferencing and pre-recorded video materials, or on-site if required. This study will help disseminate new skills.

We have not incorporated a placebo arm as it would be unethical to withhold standard care with steroids (2,8), and during participant consultation, participants said they would not accept a placebo.

### 1.2.4 Justification for choice of primary outcome

The choice of primary end-point, the improvement of pure tone audiogram average, was recommended by an international consensus meeting (2) and is used in most studies in ISSNHL. Meta-analysis suggested that the time of endpoint measurement has no effect on the change in pure tone audiogram average (10). As hearing recovery is rarely seen after 12 weeks (15), the pure tone audiogram average at 12 weeks has been chosen as the primary endpoint.

## 2 AIMS AND OBJECTIVES

The aim is to determine whether oral, intratympanic, or combined oral and intratympanic steroids is the best first line treatment for ISSNHL.

### 2.1 Internal pilot objectives

The aim of the internal pilot is to assess the ability to open sites, recruit/randomise and retain participants. Section 8.1 details the criteria that will determine continuation of the trial beyond the pilot stage.

### 2.2 Main Trial Objectives

**Primary Objectives:**

- 
- To establish the relative effects of oral, intratympanic, or combined oral and intratympanic steroids on hearing recovery in ISSNHL, when used as first line management.

#### **Secondary Objectives:**

- To complete a health economic assessment of different routes of steroid administration.
- To use participant submitted data to explore the trajectory to hearing recovery.

#### **2.2.1 Clinical Aims and Objectives**

To evaluate the clinical effectiveness of oral, intratympanic or combined oral and intratympanic steroids as the first line of treatment for ISSNHL.

#### **2.2.2 Economic Aims and Objectives**

To establish the cost-effectiveness of oral, intratympanic or combined oral and intratympanic steroids as the first line of treatment for ISSNHL.

#### **2.2.3 Exploratory Objectives**

To improve the early identification and onward referral of ISSNHL in primary care.

### **3 TRIAL DESIGN AND SETTING**

#### **3.1 Trial Design**

A pragmatic, multicentre, assessor-blinded, parallel, three-arm intervention, superiority, randomised controlled trial (1:1:1) with an internal pilot.

#### **3.2 Trial Setting**

Approximately 75 UK NHS hospitals with ENT units treating ISSNHL. Site participation will be facilitated by working with the UK ENT trainee research network, INTEGRATE.

#### **3.3 Assessment of Risk**

All clinical trials can be considered to involve an element of risk and in accordance with Birmingham Clinical Trials Unit (BCTU) standard operating procedures, this trial has been risk assessed to clarify any risks relating uniquely to this trial beyond that associated with usual care.

A Risk Assessment has been conducted and concluded that this trial corresponds to the following categorisation:

Type A = No higher than the risk of standard medical care.

### **4 ELIGIBILITY**

#### **4.1 Inclusion Criteria**

- Adults aged 18 years or over
- Diagnosis of new-onset ISSNHL- sensorineural hearing loss of 30 decibels (dBHL) or greater occurring within a 3-day period and including 3 contiguous pure-tone frequencies (out of 0.5, 1.0, 2.0, 4.0 kilohertz (kHz)) confirmed with a pure tone

---

audiogram occurring within a 3-day period (based on participant reported history)

- Onset of hearing loss within four weeks prior to randomisation
- English spoken as a first or second language

#### **4.2 Exclusion Criteria**

- Identified cause for hearing loss (not idiopathic)
- Bilateral ISSNHL
- Received prior steroid treatment for the same episode of ISSNHL
- Medical contraindication to high dose systemic steroids
- Previous history of psychosis
- On oral steroid therapy for another condition
- Known adrenocortical insufficiency other than exogenous corticosteroid therapy
- Hypersensitivity to the active substance or to any of the excipients
- Has a systemic infection unless specific anti-infective therapy is employed
- Has ocular herpes simplex
- Has ipsilateral acute or chronic active middle ear disease (including acute otitis media, chronic suppurative otitis media and cholesteatoma, excluding dry perforation)
- Does not have the capacity to provide written informed consent

#### **4.3 Co-enrolment**

Co-enrolment into other interventional trials will be considered by the Trial Management Group (TMG) on a case-by-case basis. The site should contact BCTU to seek advice prior to enrolling the participant.

### **5 CONSENT**

It is the responsibility of the Principal Investigator (PI) or delegate to obtain written informed consent for each participant prior to performing any trial related procedure. This task can be delegated by the PI to other members of the local research team, if local practice allows and this responsibility has been documented in the STARFISH site signature and delegation log.

#### **5.1 Consent Procedure**

Participants with confirmed ISSNHL will be approached about the trial by their clinical care team during the standard clinical appointment following referral to secondary care.

A Participant Information Sheet (PIS) will be provided to facilitate this process, which may be presented electronically. Participants will also be invited to watch a short explanatory video on their own smartphone, tablet or hospital computer at <https://entintegrate.co.uk/starfish>. The PI or delegate will ensure that they adequately explain the aim of the trial, trial interventions, and the anticipated benefits and potential hazards of taking part in the trial to the participant. They will also explain that participation is voluntary and that the participant is free to decide to take part and may withdraw from the trial at any time without affecting their care.

---

The participant will be given sufficient time to read the PIS and discuss their participation with others outside of the clinical or research team. The participant will be given the opportunity to ask questions before electronically signing and dating the latest version of the Informed Consent Form (ICF). Paper copies of the PIS and ICF will also be available from the Trial Office and will be printed or photocopied onto the headed paper of the local NHS Trust.

**Given the urgent need to commence treatment for the condition, randomisation and commencement of treatment should ideally occur on the same or next working day after written consent has been gained.**

## 5.2 Consent documentation

If the participant expresses an interest in participating in the trial, they will be asked to electronically sign and date the latest version of the ICF, which will be made available to all participating sites online. The PI or delegate will then electronically sign and date the ICF via the trial system. A copy of the signed ICF will be given to the participant. Should participants wish to do so, they can receive a copy of the signed ICF electronically by consenting to provide an e-mail address, or alternatively a hard copy can be provided. A copy will be filed in the medical notes and a copy placed in the Investigator Site File (ISF). Once the participant is entered into the trial, the participant's trial number will be entered on the ICF maintained in the ISF. The participant's trial number will be linked against the consent form stored in the trial database. In addition, the participant understands and acknowledges that the signed ICF will be stored in the trial database at BCTU for review.

Details of the informed consent discussions will be recorded in the participant's medical notes. This will include date of discussion, the name of the trial, summary of discussion, version number of the PIS given to the participant, version number of ICF signed and date consent received. Where consent is obtained on the same day that the trial related assessments are due to start, a note should be made in the medical notes as to what time the consent was obtained and what time the procedures started.

Electronic copies of the PIS and ICF will be available from BCTU.

## 5.3 Ongoing consent

At each visit the participant's willingness to continue in the trial will be ascertained and documented in the medical notes. Throughout the trial, the participant will have the opportunity to ask questions about the trial.

Any new information that may be relevant to the participant's continued participation will be provided. Where new information becomes available which may affect the participants' decision to continue, participants will be given time to consider and if happy to continue will be re-consented. Re-consent will be documented in the medical notes. The participant's right to withdraw from the trial will remain.

## 5.4 Additional consent

The ICF contains optional additional statements for the participant to:

- Agree that information collected about them during the study may be used to support other related research in the future, and may be shared anonymously with other researchers.

- 
- Agree to share their contact details with the STARFISH team, and to be contacted by them for up to 5 years after the trial, regarding their participation in the trial, further data collection, and to receive a summary of the trial results.
  - Agree that information held and maintained by NHS Digital and other central UK NHS bodies may be used to help contact them or provide information about their health status and medical history after the trial has ended, and agree to share their NHS number for this purpose. This will allow investigators (subject to additional funding and ethical approval) to assess longer-term impact and health service usage data without needing further contact with the trial participants.
  - Agree to use online hearing tests provided by a private company, HearX (full details are provided in section 8.3).
  - 
  - Agree to share the results of their hearing tests, but not their name, with HearX for them to use to develop a new at-home hearing test.

## 5.5 COVID-19 and trial process resilience

Participant contact throughout the informed consent process and beyond, has been designed to coincide with routine care face-to-face assessments. Appointments will take place in person at the clinic, according to local and national guidance on COVID-19.

## 6 ENROLMENT, RANDOMISATION AND BLINDING

### 6.1 Enhancing participant referral

The trial will implement the following in order to try to enhance early referral of participants with ISSNHL:

#### *GP awareness/education*

A short educational article reviewing the diagnosis and management of ISSNHL will be submitted to GP targeted publications, designed to support GPs and practice nurses. This will be authored by clinical members of the TMG. It will be used as educational material to raise awareness of ISSNHL, and will not form part of the research.

Hospital site trainee leads will provide teaching at regional GP training events, covering the assessment of hearing loss, including ISSNHL. Slides will be provided by the trial team to facilitate this. The Primary Care Academic Collaborative will also contact their 350 UK-wide members regarding the trial, asking them to promote awareness of ISSNHL and the study in their practices.

#### *ISSNHL diagnosis improvement - tuning fork assessments*

We will disseminate a validated app developed by the STARFISH team to facilitate GP assessment of participants with suspected ISSNHL. This smartphone app and associated web-based app ([entintegrate.co.uk](http://entintegrate.co.uk)) provides simple stepwise instructions on the technique for tuning fork tests, aids in interpretation, and then encourages users to refer based on the findings. If a tuning fork is not available during initial assessment or the participant is being reviewed remotely, an alternative to the Weber tuning fork test is the hum test, also described by the app. At each step, the app requests the GP to enter their findings using check boxes. These data are automatically entered into an algorithm, which on entry of the required information, informs the GP if the hearing loss may be sensorineural. The participant will not

---

have access to the app. No participant data is collected, thus avoiding data protection or NHS integration issues.

A short educational video will be made for professionals, including explaining the assessment of sudden hearing loss with tuning fork tests. This will be made available online on YouTube, accessed via a link in the app or via the website's search function. The video will also be hosted on the trial website, and cited in any GP targeted publications.

## 6.2 Identification

In line with NIHR guidance, the trial aims to improve care for underserved populations. For ISSNHL this includes those who do not present to healthcare promptly following onset of hearing loss, potentially reducing any benefit associated with steroid treatment.

### *Targeted online advertising*

ISSNHL is common in younger adults who often search social media as a source of health information. Therefore, adverts have been developed to be displayed within Facebook explaining the importance of early assessment by a clinician after any sudden change in hearing, and highlight that the STARFISH trial may be relevant to them. The adverts will be displayed following an individual entering trigger search terms such as 'hearing loss' or 'deafness'.

Effectiveness of the advertising will be assessed after the trial has been open to recruitment for six months, and further advertising stopped if fewer than 5% of participants recruited to the study sought medical help as a result of the advert.

### *Advertising design*

It is unclear what kind of messaging within the online adverts will best motivate participants to present to healthcare. Message 'framing' refers to the technique of presenting information in either a neutral (fact-based), a positive (gain-framed) or a negative (loss-framed) way. Gain-framed messages have been observed to be most effective when promoting prevention behaviours, e.g. smoking cessation and exercising regularly (16), whilst loss-framing is more effective for promoting detection behaviours, e.g. attending breast and colorectal cancer screenings (17).

As part of our aim to improve presentation to healthcare of those with ISSNHL, we have developed three different adverts that focus on using fact, gain or loss framed messaging. The three different adverts will be shown in rotation, with each shown for a month at a time, and will be used sequentially in rotation on Facebook. During the screening process, we will ask patients if they had seen the online advertising and whether it influenced them to seek medical advice with respect to their sudden hearing loss. The proportion of participants in the trial having responded to each of the three advertisements (based on timing of viewing) will be assessed to explore whether one form of message framing is superior at prompting participants to seek medical help. The results of this work will help to inform discussion at planned ISSNHL focus groups which will be set up as an independent study once the trial is underway. These focus groups will explore barriers and facilitators to accessing healthcare for ISSNHL.

---

Additionally to the advertising, the trial participant group and PPI lead manage a Facebook peer-support group for ISSNHL to provide more information on the condition and the trial.

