## 8 OUTCOME MEASURES

### 8.1 Internal Pilot Outcome

The success of the 9-month internal pilot study will be based upon the recruitment rate, adherence to the treatment allocation and dropout rate. At 9 months, it is anticipated that the trial will have recruited 81 participants from at least 36 centres. For the trial to continue pre-defined stop-go criteria must be met. A traffic light system has been designed to determine continuation to the full trial:

**Green:** Recruitment rate  $\geq 100\%$ , adherence rate  $\geq 90\%$ , and dropout rate  $< 5\%$ . If all three criteria are met, the trial will continue with the protocol unchanged.

**Amber:** Recruitment rate 70-99%, adherence rate 70-89%, or dropout rate 5-10%. If one or more of the criteria are met, the trial will be reviewed to determine the changes (if any) that could be made to improve whichever criteria are not at the green level.

**Red:** Recruitment rate  $< 70\%$ , adherence rate  $< 70\%$ , or dropout rate  $> 10\%$ . If one or more of these criteria are met, this will be discussed with the Trial Steering Committee (TSC) and funder regarding feasibility of the trial continuing.

**Table 1:** Internal pilot progression criteria

|                         | Red  | Amber   | Green |
|-------------------------|------|---------|-------|
| Recruitment threshold   | <70% | 70%-99% | ≥100% |
| Adherence threshold     | <70% | 70%-89% | ≥90%  |
| Drop-out rate threshold | >10% | 5-10%   | <5%   |

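### The three framed adverts are shown one month at a time and compared by share of trial participants, so message is confounded with month and open sites, and the described screening question cannot identify the advert seen (minor; exploratory aim only)

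*Protocol*

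**What the plan says.** Protocol section 6.2 (Advertising design) states "we have developed three different adverts that focus on using fact, gain or loss framed messaging". They run "with each shown for a month at a time, and will be used sequentially in rotation on Facebook". No concurrent display, randomised order or regional split is described.

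Data come from a question at screening: "we will ask patients if they had seen the online advertising and whether it influenced them to seek medical advice". The analysis is then: "The proportion of participants in the trial having responded to each of the three advertisements (based on timing of viewing) will be assessed". The declared purpose is to explore whether one framing is superior at prompting people to seek help, and the result is to feed focus groups run as a separate study.

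Under Targeted online advertising, the same section sets a check after six months of recruitment, with "further advertising stopped if fewer than 5% of participants recruited to the study sought medical help as a result of the advert". Section 8.1 gives the expected build-up at nine months: "it is anticipated that the trial will have recruited 81 participants from at least 36 centres". Section 3.2 plans about 75 sites in all.

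**The concern.** Each message is tied to its own months. Anything else that differs between those months, such as the number of open sites or other publicity, is mixed with the effect of the framing. Sections 6.1 and 6.2 also run GP education, posters and charity publicity.

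The chosen measure does not separate them. A share of all trial participants is neither a response per person shown the advert nor a response per patient presenting while it ran. An advert shown when more sites are recruiting can collect more responders without being more persuasive.

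Two further gaps concern who is counted and how:

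- Attribution by time of viewing needs a viewing date or the advert version. The screening question as described covers only whether the advertising was seen and whether it influenced the patient.
- The question goes to patients at screening, but the analysis counts participants in the trial. Responders who prove ineligible or decline are lost. They include people beyond the four-week onset limit in section 4.1, although section 6.2 names those who do not present promptly as the underserved group.

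At stake is a misleading ranking of the three messages passed on to the focus groups. Randomisation, the primary outcome and safety are not affected.

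**Working it through.** The protocol gives no sample size or expected difference for the advert comparison, so there is no figure of its own to reproduce. The check asks how unequal the adverts' months would be if framing had no effect.

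**Inputs from the protocol.** Three adverts, one month each, in rotation (6.2); 81 participants at month 9 (8.1); about 75 sites (3.2) and at least 36 centres at month 9 (8.1); 525 participants in total (14.1); advertising check at six months with a 5% threshold (6.2).

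**Assumptions.** The adverts keep a fixed order from month 1. Monthly recruitment rises linearly, 1.8 × k in month k, because 1.8 × (1 + 2 + … + 9) = 1.8 × 45 = 81. The document gives neither monthly accrual nor recruitment duration.

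**Recruits falling in each advert's months, no message effect**

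| Horizon | Advert 1 | Advert 2 | Advert 3 | Third ÷ first |
|---|---|---|---|---|
| 6 months (total 37.8) | 1.8 × (1+4) = 9.0 | 1.8 × (2+5) = 12.6 | 1.8 × (3+6) = 16.2 | 1.80 |
| 9 months (total 81) | 1.8 × 12 = 21.6 | 1.8 × 15 = 27.0 | 1.8 × 18 = 32.4 | 1.50 |
| 36 months, rate flat at 16.2 after month 9 (total 518.4) | 21.6 + 9 × 16.2 = 167.4 | 172.8 | 178.2 | 1.06 |
| 24 months, rise continues to 75 sites, then flat (total 510.3) | 159.3 | 170.1 | 180.9 | 1.14 |
| 24 months, rise never levels off (total 540) | 1.8 × 92 = 165.6 | 1.8 × 100 = 180.0 | 1.8 × 108 = 194.4 | 1.17 |

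The fourth row takes 36 ÷ 9 = 4 new sites a month, so 75 sites at month 18.75 and a ceiling of 1.8 × 18.75 = 33.75 recruits a month. The imbalance is large early and small once many cycles are averaged.

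**Calendar.** Because 3 divides 12, a fixed order puts the adverts in trial months 1, 4, 7, 10; 2, 5, 8, 11; and 3, 6, 9, 12 of every year. More years do not change this. Each advert does fall once in every quarter, so broad season is balanced over a full year.

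**Number of responders.** At the 5% threshold, 0.05 × 525 gives about 26 responders in the whole trial, and 0.05 × 37.8 = 1.9 at the six-month check. A three-cell chi-square test at the 5% level has simulated power of about 0.32 to detect a true 50/25/25 split with 26 responders, 0.60 with 52 and 0.90 with 105.

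**The case against.** The strongest reply is that this is a side question. The text promises only to explore, the result informs discussion in a separate study, and repeated rotation averages out most of the site build-up over a full trial. That stands, and it sets the severity. It does not supply the missing viewing date or version, and it gives little comfort if advertising ends at six months after two cycles.

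Four stronger readings are tempting but not supported.

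- *Responses spill into the next advert's month.* A delay between viewing and screening misclassifies only if month of screening is used. The plan assigns responses by time of viewing, and it gives no distribution for that delay. The real gap is that the described question does not capture the date.
- *With equal messages the last advert will look best.* The counts above are all recruits, not responders. With about 6 responders (8% of 81), the third advert is strictly highest only about 40% of the time, so chance dominates.
- *The four-week onset limit favours one message.* It applies equally to all three. It narrows who is counted but does not bias the comparison between adverts.
- *The 5% rule should wait for 81 participants.* If advertising truly brings 8% of participants, the chance of stopping is 0.205 with 36 recruited (at most 1 responder), 0.183 with 54 (at most 2) and 0.214 with 81 (at most 4). Waiting does not reduce the risk.

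It is also fair to object that concurrent display may expose one person to several messages, and that asking which version was seen relies on recall.

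**Conclusion.** The concern holds as a minor design defect confined to the exploratory framing comparison in section 6.2. Message is confounded with month and number of open sites, the denominator does not adjust for this, the described question records neither version nor viewing date, and responders who are screened but not enrolled are omitted.

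The build-up imbalance is about 1.5-fold at nine months and 1.8-fold at six, falling to about 1.06 to 1.17 over the whole trial. These figures rest on the assumed accrual and fixed order; only the 81 participants, the centre counts and the 525 come from the protocol.

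A reader might infer that the framing work is worthless. That goes too far: a descriptive account remains possible. What the design cannot support is a conclusion that one framing is superior.

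**What to change.** In section 6.2:

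1. Show the three adverts concurrently with equal random allocation by the platform. Failing that, randomise their order within each three-month block.
2. Add to the screening question which version was seen and when.
3. Count responders among all screened patients, not only those randomised. Express them relative to adverts delivered under concurrent display, or to patients screened in the same period under blocked order. The screening log in section 6.3 already carries the date of screening.
4. If none of this is done, report the responses descriptively and remove the reference to superiority.

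Leave the timing of the 5% check as it is.

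The cost is an advert setting and one screening item. The remaining weaknesses are recall of the version seen and some people seeing more than one message.
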